### Interim analyses {21b}

There are no interim analyses and stopping guidelines planned for this study. PI and sponsor can make the final decision to terminate the study.

### Methods for additional analyses (e.g., subgroup analyses) {20b}

Secondary analyses and subgroup analyses are currently being developed. We are planning to do subgroup analyses of standardized assessment data (e.g., mood and craving), daily diaries, and NRT use.

### Methods in analysis to handle protocol non-adherence and any statistical methods to handle missing data {20c}

We anticipate minimal missing data (< 5%) for the primary outcome (day 7 smoking status) due to our daily contact with participants during the treatment phase. We will evaluate the effects of missingness by calculating differences across plausible and extreme missing-data scenarios. If our primary test is significant, we will also calculate the size of the interaction between the group and missingness that would be required to make this difference non-significant. If missing data causes the exclusion of 10% or more of the baseline sample, we will conduct an analysis using multiple imputation. In our imputation models, we will include the variables from our primary analysis, biochemically verified quit status, data on craving, and NRT use at all available time points.

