The research team will mail each participant a study kit consisting of a 6-week supply of NRT (patches plus gum or lozenge) and dried blood spot collection kits. Participants who smoke 10 or more cigarettes per day will receive 4 weeks of 21 mg and 1 week each of 14 mg and 7 mg nicotine patches, while those smoking 5–9 cigarettes per day will receive 4 weeks of 14 mg and 2 weeks of 7 mg nicotine patches. Nicotine patches will be pre-organized into weekly packages, requiring the participants to reduce the dosage from 21 mg or 14 mg to 7 mg throughout the 6-week treatment period. All groups will be instructed to collect a dried blood spot and start using their NRT on their target quit date, as well as attempt to be completely abstinent from smoking starting from their target quit date onwards. Dried blood spots will be used to measure blood cotinine levels to confirm participants’ smoking status. Participants will be instructed to apply a new patch every day and use 2 mg nicotine gum or lozenge as needed to curb any urges to smoke. The research team will provide each participant with 2 packs of nicotine gum in which the maximum dosage is 30 pieces a day. These combinations and dosages of NRT have been found most effective for smoking cessation [17].

Participants will also have access to the behavioral support videos and handouts from the time they receive their welcome e-mail until the end of the study. Participants will be asked to complete daily diaries and weekly questionnaires to document tobacco use, NRT use, nicotine craving and withdrawal symptoms, mood, adverse events, and menstrual cycle symptoms via online REDCap surveys. Additional questionnaires will include Patient Health Questionnaire [18] (PHQ-9; weeks 1 and 6), Positive Affect and Negative Affect Schedule – Short Form [19] (PANAS-SF; weeks 1–6), Minnesota Nicotine Withdrawal Scale [20] (MNWS; weeks 1–6), and Perceived Stress Scale 4 [21] (PSS-4; weeks 1–6). Smoking status will be assessed at the end of weeks 1 and 6; those who self-report continuous abstinence from smoking for at least 7 previous days will be asked to collect dried blood spots and mail them within 3 days of collection (for biochemical verification of abstinence). At the end of treatment (week 6), participants will also be asked to complete a study satisfaction survey. Refer to Fig. 1 for a brief overview of the study and to Fig. 2 for a detailed schedule of events.

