#### Strategies to improve adherence to interventions {11c}

Daily diaries and weekly questionnaires will be programmed for automatic delivery in REDCap, based on the target quit date of the participant. Participants will also be notified about their target quit date and receive reminders to complete their baseline assessments, daily diaries, and weekly questionnaires. Reminders and notifications will be sent via email and/or SMS texts. If a participant does not provide information pertaining to the primary outcome of the study (quit status on day 7), the study staff will attempt to follow up with them.

As an incentive to complete and mail back dried blood spot collections, we will compensate participants with a $5 e-gift card for each dried blot spot collection received. Thus, all participants are eligible to receive at least one $5 e-gift card (baseline assessment) and can receive up to a total of $20 in e-gift cards throughout the study (up to 4 blood spots can be collected depending on whether participants achieve abstinence from smoking).

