### Outcomes {12}

#### Primary outcome

We are primarily interested in the between-group comparison of proportions of biochemically confirmed abstinence, measured through dried blood spots, at 7 days post-target quit date. The trial will be considered successful if the proportion of abstinent participants in either of the groups with a target quit date based on the menstrual cycle phase (follicular or luteal) is significantly higher than in the usual practice group.

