### Data collection and management

#### Plans for assessment and collection of outcomes {18a}

Quit status at day 7, week 6, and 6 months post-target quit date will be assessed using REDCap questionnaires designed by the research team (see Additional file 1). These repeated assessments at different time points will allow us to track the participants’ quit status longitudinally and assess both short- and long-term outcomes. If a participant reports abstinence from smoking, their abstinence will be confirmed biochemically using dried blood spot analysis. Collecting dried blood spots is minimally invasive, cost-effective, and ideal for home sampling when conducting population-based research [22]. Filter paper blood collection demonstrates the same level of precision and reproducibility as standard methods of collecting blood [23], and the results are precise for cotinine [24], progesterone, and estradiol [25]. Additionally, the participants will be directed to complete daily diaries designed by the research team in REDCap (see Additional file 2) to provide data about their day-to-day smoking status and NRT use. The participants will also complete baseline and weekly standardized assessments of mood (PHQ-9 [18] and PANAS-SF [19]), nicotine withdrawal symptoms (MNWS [20]), and perceived stress (PSS-4 [21]). An analysis plan for daily diaries and standardized assessments is currently being developed.

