#### Plans for collection, laboratory evaluation, and storage of biological specimens for genetic or molecular analysis in this trial/future use {33}

Dried blood spot will be collected on the first and last days of NRT treatment and on day 7 of NRT treatment. Dried blood spots will determine the progesterone and estrogen levels to confirm the phase of the menstrual cycle and determine cotinine concentration levels to confirm smoking status. Participants will perform the collection procedure independently. Drops of whole blood are collected on filter paper from a finger prick with a single-use lancet following sterilization with isopropyl alcohol. Blood drops are left to dry for at least 4 h or overnight, and the filter paper matrix stabilizes the analytes in the dried blood spot at room temperature [22]. Dried blood spots provided by the participants will be stored at − 80 °C in the freezer at a designated CAMH facility prior to biochemical analysis at a University of Toronto-affiliated laboratory and will be destroyed after they are analyzed.

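### Day-7 blood spots are requested only from self-reported abstainers, yet the imputation model omits self-reported smoking and no rule covers an unreturned spot

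*Protocol article*

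**What the plan says.** The primary outcome compares "proportions of biochemically confirmed abstinence, measured through dried blood spots, at 7 days post-target quit date" (Primary outcome). Under Intervention description {11a}, the request for a spot at the week 1 and week 6 checks is conditional: "those who self-report continuous abstinence from smoking for at least 7 previous days will be asked to collect dried blood spots". Two other sections agree: "If a participant reports abstinence from smoking, their abstinence will be confirmed biochemically using dried blood spot analysis" ({18a}) and "up to 4 blood spots can be collected depending on whether participants achieve abstinence from smoking" ({11c}). Section {33} words it without a condition: "Dried blood spot will be collected on the first and last days of NRT treatment and on day 7 of NRT treatment".

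On missing data, {20c} does four things:
- It forecasts under 5% missing "for the primary outcome (day 7 smoking status) due to our daily contact with participants".
- It plans plausible and extreme missing-data scenarios.
- It plans, if the primary test is significant, a calculation of how strong a group-by-missingness interaction would have to be to remove significance.
- It plans multiple imputation if 10% or more of the baseline sample would be excluded, in which "we will include the variables from our primary analysis, biochemically verified quit status, data on craving, and NRT use at all available time points".

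The primary-analysis variables in {20a} are group, outcome, age, income and the heaviness of smoking index. Section {18b} adds that participants who miss the week 1 and week 6 questionnaires and any required spots are withdrawn and their data are not kept.

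**The concern.** A participant who reports smoking at day 7 is not abstinent, and no spot is needed to know it. A participant who reports abstinence has a verified outcome only if a home finger-prick sample is taken and mailed back. Missingness caused by spot non-return therefore depends on self-report, which is closely tied to the outcome itself.

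The plan does not use this. Below the 10% trigger, the wording about exclusion implies that the logistic models run on participants with data. At or above it, the imputation model leaves out the variable that the design makes the driver of missingness, although the day-7 questionnaire and the daily diaries collect it. The forecast of under 5% rests on daily contact, which secures self-report; mailing a spot is a separate step for which no return rate is given.

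At stake are the absolute quit rates, the risk difference and power. The comparison itself would also be at risk if spot return differed between arms.

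**Working it through.** **The plan's own figure.** Inputs from Sample size {14}: 25% against 34%, about 400 per arm; two-sided 5% is assumed. Power = Φ[(0.09 − 1.96 × SE0)/SE1], with SE0 = √(2 × 0.295 × 0.705/400) = 0.0322 and SE1 = √((0.25 × 0.75 + 0.34 × 0.66)/400) = 0.0321. This gives 79.8%, so the stated 80% reproduces.

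**Set-up.** Let p be the true verified rate, v the share of self-reported abstainers who would verify, and r the spot return among them. The documents give neither v nor r, so both are assumptions. All questionnaires are taken as completed.
- Self-reported abstinent: s = p/v
- Missing: s(1 − r)
- Rate among those with data: p·r / [1 − s(1 − r)]

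**What the forecast implies.** The mean of 25%, 25% and 34% is 28%. If all missingness is spot non-return, 5% missing means 1 − r = 0.05v/0.28, or 14–18% of self-reported abstainers without a spot for v from 0.8 to 1.0. So a forecast of under 5% needs spot return of at least about 82–86%.

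**Equal return of 80%.** Worked for v = 0.9: s = 27.8% and 37.8%; missing 5.6% and 7.6%; rates 0.200/0.9444 = 21.2% and 0.272/0.9244 = 29.4%.

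| v | Missing, usual practice / better arm | Rates | Difference | Odds ratio | Power |
|---|---|---|---|---|---|
| 0.8 | 6.3% / 8.5% | 21.3% / 29.7% | 8.4 points | 1.56 | 74.7% |
| 0.9 | 5.6% / 7.6% | 21.2% / 29.4% | 8.2 points | 1.55 | 73.8% |
| 1.0 | 5.0% / 6.8% | 21.1% / 29.2% | 8.1 points | 1.545 | 73.1% |

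The true odds ratio is (0.34/0.66)/(0.25/0.75) = 1.545. Over three arms, 5.6–7.0% are missing, so imputation is not triggered. With v = 1 the odds among those with data are p·r/(1 − p); r cancels between arms and the odds ratio is exactly preserved.

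**Above the trigger.** A large-sample imputation took v = 0.9, about 12% missing overall, and one auxiliary variable standing in for craving and NRT use, assumed to shift by 0.8 SD with self-report.
- Those with data: 17.2% and 24.5%
- Imputed without self-report: 18.0% and 25.6%
- Imputed with self-report: 25.0% and 34.0%

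A second run at 60% return also used week-6 verified status, which {20c} does list, again under assumed associations. It gave 19.9% and 28.2% without self-report, and 25.1% and 34.0% with it. Without self-report the odds ratios are about 1.57 and 1.58, so here too the absolute rates suffer and the odds ratio does not.

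**Unequal return, no true effect (25% in both arms, v = 0.833).** The rejection rate is Φ(d/SE − 1.96) plus a negligible opposite tail. For 80% against 60% return: rates 21.3% and 17.0%, d = 4.2 points, SE = √(0.2128 × 0.7872/376 + 0.1705 × 0.8295/352) = 2.9 points, rejection about 31%. For 90% against 80% it is about 10%; for 85% against 80%, about 6%. Across v from 0.8 to 1.0 the first figure ranges from 30% to 33%, and the others move by less than one point.

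**The case against.** The strongest reply is that an unreturned spot may not be missing at all. The outcome is confirmed abstinence, so an unconfirmed report could simply count as not abstinent, and the gloss of the outcome as day-7 smoking status, with its daily-contact rationale, fits that reading. This stands to the extent that analysis of those with data is inferred, not stated. But the article does not state the missing-equals-smoking rule either. If it were applied, 80% return would give 20.0% and 27.2% and power of 67%, so the choice matters and should be written down.

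Second, {20c} is not silent on sensitivity. The scenarios and tipping-point calculation would expose dependence on the missing spots. They leave the primary estimate and the imputation model as they are, and the tipping-point step runs only after a significant result.

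Third, a reader might infer that the planned treatment effect is attenuated. That does not hold on the scale of the planned logistic model when return is equal: the odds ratio stays at 1.545–1.56. Power falls because there are fewer events and fewer participants analysed.

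Fourth, a reader might infer that the type I error is inflated. That needs unequal return, for which the documents give no basis: all arms have the same kit, reminders and incentive, and {11b} expects no systematic difference in discontinuation. The figures above are scenarios.

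Finally, unanswered questionnaires are another route to missing data, one that does not pass through observed day-7 self-report. Diary reports would still inform those cases.

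**Conclusion.** The point holds in a limited form. Requesting spots on self-report makes non-return a problem confined to likely abstainers. The listed imputation variables omit self-report, imputation starts only at 10%, and an unreturned spot has no stated primary rule. The trigger and the variable list are fixed in this article, so this is more than a detail left to an analysis plan.

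Under equal 80% return, the cost is roughly 4–5 percentage points on each arm's quit rate, 0.6–0.9 points on the risk difference, and 5–7 points of power. It leaves the modelled odds ratio essentially intact. These sizes rest on assumed return and verification shares and on reading exclusion as analysis of those with data. A spurious group difference is possible only if return differs by arm. The change is worth making because it uses data already planned for collection.

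**What to change.** 1. Add self-reported smoking status (day-7 and week-6 questionnaires and daily diary) to the imputation model for the verified outcome.
2. State the primary rule for a self-reported abstainer without a spot. Preferably impute within the self-reported-abstinent stratum whatever the overall missing percentage, with missing-equals-smoking as a sensitivity analysis. Keep the planned scenarios and tipping-point calculation.
3. Reconcile this with {18b}, under which the data of some non-returners are not kept and so could not be imputed. Align the unconditional wording in {33} with {11a}, {11c} and {18a}.
4. Secondary: base the missing-data forecast on spot return, and report return among self-reported abstainers by arm.

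The cost is wording and a little more analysis, with no new data collection. Item 3 may need a change to the retention rule as well as to the statistical text.

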### Plans to give access to the full protocol, participant-level data, and statistical code {31c}

Anonymized participant data may be shared for use in other studies. There are no intentions to grant public access to protocol and statistical code.

### Oversight and monitoring

#### Composition of the coordinating center and trial steering committee {5d}

The day-to-day management group will consist of the PI, a doctoral student, a research coordinator, an assistant manager, and seasonal research placement students. The group will meet weekly. This study does not have a Trial Steering Committee.

#### Composition of the data monitoring committee, its role, and reporting structure {21a}

A Data Monitoring Committee (DMC) is not required, as there are no interim analyses, no planned procedures for early stopping, and the treatment used (NRT) is available over the counter.

#### Adverse event reporting and harms {22}

Adverse events will be collected daily and weekly via REDCap surveys and reviewed by the study investigators for any serious or unexpected adverse events. Applicable serious unexpected adverse events (SAEs) will be recorded and reported to REB in accordance with REB requirements and timelines.

#### Frequency and plans for auditing trial conduct {23}

The PI and site will permit study-related audits, and inspections by the REB, CAMH, sponsor, and applicable granting agencies or regulatory bodies, including access to all study-related documents (e.g., source documents, regulatory documents, data collection instruments, study data). The PI will ensure the capability for audits/inspections of applicable study-related facilities (e.g., research pharmacy, clinical laboratory, imaging facility).

#### Plans for communicating important protocol amendments to relevant parties (e.g., trial participants, ethical committees) {25}

No deviations from or changes to the protocol will be implemented without prior agreement from the sponsor as required, and approval from the REB, unless to eliminate an immediate hazard to a participant.

#### Dissemination plans {31a}

The PI will hold primary responsibility for the publication of the results of this clinical trial. Publications will be prepared in compliance with CAMH Policy AR 1.17 (Research Publications).

## Discussion

The majority of quit attempts are unsuccessful [6], with women demonstrating lower quit success than men [9]. This study aims to close this gap by investigating a new intervention to improve quit outcomes in individuals with menstrual cycles. We propose an intervention of coordinating the start date of NRT either to the mid-follicular or mid-luteal phase of the menstrual cycle. Although there is a body of research on smoking cessation relative to the menstrual cycle, previous studies report equivocal findings and are limited by small samples and a lack of clarity regarding ideal quit date timing [11–13]. This trial will overcome these limitations by recruiting a large sample of participants and limiting the target quit date to the middle of both the follicular and luteal phases. Through this online trial with minimally invasive interventions, participants will have free access to long- and short-acting NRT along with behavioral support, proven to be one of the most effective combination treatment strategies for smoking cessation (with the two interventions demonstrating higher efficacy when used together, rather than alone) [27, 28]. Therefore, participants will have a higher chance of quitting relative to unaided attempts, regardless of group allocation. The timing interventions will be compared to usual practice. The results of the trial can inform the recommendations to further explore the effects of the menstrual cycle on smoking cessation outcomes. The findings could also provide evidence for the implementation of menstrual cycle phase timing strategies in smoking cessation programs.

The challenge that the trial team has encountered so far is a delay in the trial timeline, resulting from an extended time period to get REB approval and prepare for participant recruitment. Some potential future limitations of this study may include loss to follow-up and missingness of data due to the online nature of the study. Loss to follow-up can be prevented by email and SMS reminders, as well as gift card incentives to complete dried blood spot collections. Missingness of the data will be accounted for in the statistical analysis.

Overall, coordinating the start of NRT to the menstrual cycle phase can be an easy, accessible, low-risk, and low-cost method of improving the quit success rate in a large proportion of smokers. This randomized clinical trial can inform further preventative measures to improve smoking outcomes in premenopausal individuals, therefore having a positive impact on the incidence of smoking-related disease.

## Trial status

The original version of the protocol (version 1.1 dated May 6, 2022) was approved by CAMH REB on June 9, 2022. The ethical approval document is provided in Additional file 3. Current version 1.2 (dated October 4, 2022) was approved by CAMH REB on November 8, 2022. The trial was registered on ClinicalTrials.gov on August 23, 2022. Recruitment commenced on November 30, 2022, and is expected to be completed in 2024.

## Data Availability

The datasets generated or analyzed during the current study are available from the corresponding author upon reasonable request.

## Abbreviations

AE: Adverse event
BHDB-RR: BrainHealth Databank Research Resource
CAMH: Centre for Addiction and Mental Health
HSI: Heaviness of smoking index
IUD: Intrauterine device
MNWS: Minnesota Nicotine Withdrawal Scale
NDS: Nicotine Dependence Services
NRT: Nicotine replacement therapy
PANAS-SF: Positive Affect and Negative Affect Schedule – Short Form
PHI: Personal health identifiers
PHQ-9: Patient Health Questionnaire-9
PI: Principal investigator
PSS-4: Perceived Stress Scale 4
REB: Research Ethics Board
REDCap: Research Electronic Data Capture
SAE: Serious adverse event
SOPs: Standards of operation
STOP: Smoking Treatment for Ontario Patients
